## Abstract

**Background:**

Preterm infants are at risk for neurodevelopmental disorders, including motor, cognitive or behavioural problems, which may potentially be modified by early intervention. The EU CareToy Project Consortium (http://www.caretoy.eu) has developed a new modular system for intensive, individualized, home-based and family-centred early intervention, managed remotely by rehabilitation staff. A randomised controlled trial (RCT) has been designed to evaluate the efficacy of CareToy training in a first sample of low-risk preterm infants.

**Methods/Design:**

The trial, randomised, multi-center, evaluator-blinded, parallel group controlled, is designed according to CONSORT Statement. Eligible subjects are infants born preterm without major complications, aged 3-9 months of corrected age with specific gross-motor abilities defined by Ages & Stages Questionnaire scores. Recruited infants, whose parents will sign a written informed consent for participation, will be randomized in CareToy training and control groups at baseline (T0). CareToy group will perform four weeks of personalized activities with the CareToy system, customized by the rehabilitation staff. The control group will continue standard care. Infant Motor Profile Scale is the primary outcome measure and a total sample size of 40 infants has been established. Bayley-Cognitive subscale, Alberta Infants Motor Scale and Teller Acuity Cards are secondary outcome measures. All measurements will be performed at T0 and at the end of training/control period (T1). For ethical reasons, after this first phase infants enrolled in the control group will perform the CareToy training, while the training group will continue standard care. At the end of open phase (T2) all infants will be assessed as at T1. Further assessment will be performed at 18 months corrected age (T3) to evaluate the long-term effects on neurodevelopmental outcome. Caregivers and rehabilitation staff will not be blinded whereas all the clinical assessments will be performed, videotaped and scored by blind assessors. The trial is ongoing and it is expected to be completed by April 2015.

**Discussion:**

This paper describes RCT methodology to evaluate CareToy as a new tool for early intervention in preterm infants, first contribution to test this new type of system. It presents background, hypotheses, outcome measures and trial methodology.

**Trial registration:**

ClinicalTrials.gov: NCT01990183. EU grant ICT-2011.5.1-287932.

## Background

The incidence of preterm births has increased and survival rates in very preterm infants have improved over the past two decades [1, 2]. However, a significant number of these infants, especially if born with a very low birth weight (VLBW), show a developmental disorder. Follow-up studies indicate that up to 15% of infants are diagnosed with cerebral palsy and about 50% show cognitive, motor, or behavioural problems in childhood [3–5], resulting in a lower high school graduation rate compared with infants born at term with normal birth weight [6].

Early developmental interventions have been used in the clinical setting with the aim of improving the overall outcome for preterm infants [7]. Early Intervention (EI) means intervening as soon as possible to tackle problems that have already emerged due to perinatal or congenital brain disorders. It is carried out in a critical period of development (i.e. a time window during which specific functions develop very rapidly), when initial signs of atypical development are present but before they become overt. The target of EI training is to strengthen brain plasticity, higher in the first years of life, and to allow a better functional outcome. According to the neuroscience evidences, the activity-dependent neural plasticity is able to mould the neural development mainly during the critical periods, as indicated by several examples especially for motor and visual systems, both in animal models and in infants with brain lesion [8–12].

Based on our current neurobiological understanding, EI programs have to be implemented very early in life and should be intensive, repetitive, incrementally challenging, and individualized. They should include also goal-directed components and exercises where meaningful goals are provided, to give opportunities for problem solving and to indirectly drive the movements required to successfully meet task demands [13, 14]. The therapeutic approach should also involve repeated practice of tasks, which the infant wants to do [15]. There is also accumulating evidence of the importance of an enriched environment (EE) on infant's neurodevelopment [16–20]. Home EE should be organized to encourage the infant to perform specific tasks, tailored on the developmental needs of the individual infant, in an environment where the parent is actively and positively engaged with the child, to facilitate and promote learning. The home environment should include safe toys appropriate to the infant's ability level but posing a learning challenge and family interactions. In this context, as proposed by Morgan et al. [21], EE intervention could be defined as a set of modifications aimed to enrich motor, cognitive, sensory, or social aspects of the infant’s environment with the purpose of promoting learning.

Systematic and Cochrane Reviews [5, 22, 23] indicate an evidence of the positive effects of EI, mainly based on parents involvement, on the development of cognitive and motor functions in preterm infants. However, the identification of the most effective intervention strategies is difficult and more RCT, including control groups, with well defined content, focus, duration and intensity are deeply needed.

Moreover, providing infants at high risk of neurodevelopmental disorders by an EI personalized and with significant intensity and duration would impose high costs for the Health Care System. Even in western countries resources are unlikely to be sufficient to cover all needs. Moreover, some families have difficulties, for different reasons, to reach health care services. Biotechnologies, tele-rehabilitation and eHealth could represent a promising approach to provide home EI programs for a large number of infants at a relatively low cost.

On this background, the CareToy Project (http://www.caretoy.eu, Trial Registration: NCT01990183) has aimed to develop a new technological smart modular system as a tele-rehabilitation tool for EI in infants at risk for neurodevelopmental disorder. The CareToy system for EI, called CareToy Home is composed by four modules: 1) *gym module* made of i) a kit of sensorized toys with different shape and size, ii) two interactive walls (feedback wall with embedded sounds and lights), iii) a belt wall with a sensorized pillow, iv) an arch with lights, v) 4 cameras; 2) *vision module* (screen wall), equipped with a large monitor; 3) *mat module* with a sensorized mat and three wearable sensors (two bracelets and chest strap) [24, 25] and 4) *tele-rehabilitation module* that allows the communication between CareToy system and clinical centre (Figure 1A).

**Figure 1 Fig1:**
[figure not shown]
**CareToy for Home and CareToy for Clinics. A**, 1) Set up of CareToy for Home (*CareToy H*). It is delivered at home and used to promote infants’ motor and perceptual development, through individualized goal directed activities (rehabilitation packages of CareToy training). 2) Kit of sensorized toys. 3) The four modules of CareToy H (Gym, Vision, Mat and Tele-rehabilitation). **B**, 1) CareToy for Clinics (*CareToy C*), installed at the rehabilitation centres. 2) Reconstruction of the gaze of an infant during the observation tasks.

The software includes principles, procedures and computer algorithms for data acquisition, processing and sensory integration from various sensors. Signal processing is performed in two different modes: i) real-time processing that provides information relevant for generating immediate feedback to the infant based on his/her activity and ii) post-processing of data that allows more detailed off-line analysis of the infant’s behaviour.

CareToy allows an intensive, individualized, home-based and family-centred intervention, managed remotely by trained clinical staff. The rehabilitative staff may use the modular organization and the possibility of activating single parts of the system (e.g. there are many lights in the wall but they are hidden and they can be variously activated associated or not with sounds/music) automatically and/or in relation to the actions of the infant (e.g. only if the infant rolls or grasps) to tailor the training to the individual needs of the infant. The infant may in this way be promoted to actively perform specific goal-directed activities (e.g. for postural control, reaching, grasping, visual attention and orientation). Feedback regarding the performance of the infant is obtained by video and sensors in toys and mattresses. They provide quantitative information about grasp shape and force, orientation and displacement in space of toys and postural changes of the infant. Acquired data are automatically uploaded to a clinical database server through the tele-rehabilitation module. This also allows the rehabilitation staff to manage the training remotely, plan new individualized exercises, assess the validity of the exercises and create and update new exercises. The CareToy training in this way guarantees a highly variable and individualized approach, tailored on the specific needs of the infant and on the achievement of specific goals.In the context of the CareToy project a platform for the quantitative evaluation of visual abilities has been also developed. This is named CareToy for Clinics and it is a highly advanced system, which is installed in the clinical centres and used only by expert rehabilitation staff. It consists of an eye tracking system (Smart Eye Pro system) equipped with 6 external infrared cameras running at 60 Hertz placed in an integrated mechanical structure with 5 screens and 5 loudspeakers (placed one in the centre, two on the right side at 30° and 60° and two on the left side, also at 30° and 60°) (Figure 1B).

To test the effects of the CareToy training on infant’s neurodevelopment we propose a randomised controlled trial (RCT) in a population of low risk preterm infants. The trial fulfils the criteria set out in the Consolidated Standards of Reporting Trials (CONSORT) Statement for Randomised Trials of non-pharmacologic treatment guidelines [26, 27].

## Methods/Design

The following hypotheses will be tested in the RCT:

 CareToy training may improve the neurodevelopmental (e.g. motor, perceptual and cognitive) outcome in preterm infants; CareToy training may help caregiver, whose role is essential for EI, in assisting skill development in their child by adapting the physical and play environment of the system; CareToy system, with the characteristics pointed out above, designed and carried out in the CareToy project with also tele-rehabilitation and ICT strategies, could represent a novel home-based, rehabilitation setting for infants born preterm or at risk for neurodevelopmental disorders, for their families and for health system.

These experimental hypotheses will address the following specific aims:To provide first evidences that CareToy, compared to standard care, is useful to promote neurodevelopment in low risk preterm infants.To stimulate, by CareToy training, the caregiver-infant interaction during play activities.To provide evidence that the CareToy system is a suitable tool for an enriched and playful EI setting at home. If these aims will be achieved in low risk preterm infants, CareToy may be proposed as a new rehabilitation tool for infants at high risk of developing neurodevelopmental disorders.

### Study design

A multicenter, evaluator-blinded, parallel group RCT will be carried out to compare the effects of the CareToy training to standard care in preterm infants.The two clinical centres involved in the study are the IRCCS Fondazione Stella Maris, Department of Developmental Neuroscience, in Pisa (Italy), in collaboration with Neonatal Intensive Care Unit, Pisa University Hospital “Santa Chiara” and in Copenhagen (Denmark) the Helene Elsass Center, in collaboration with the University of Copenhagen (Depts. of Neuroscience and Pharmacology and Neonatology, Rigshospitalet). Clinical assessment will be performed at baseline (T0, in the week preceding the CareToy intervention/standard care) and in the week after the end of CareToy training/standard care (T1, primary endpoint). For ethical issues, after T1, the infants who start with standard care will have the opportunity to receive the CareToy training, while the infants that have already performed CareToy training will continue standard care. At the end of this open phase (T2), all the infants will be assessed as at T1. Moreover, a further assessment will be performed at 18 months of corrected age (T3) to evaluate the long-term effects on neurodevelopmental outcome. The experimental design and the timeline are described in detail in Figure 2. A pilot study has been performed in order to assess the feasibility of the CareToy training and to tune and set-up the CareToy system and the rehabilitation packages.

**Figure 2 Fig2:**
[figure not shown]
**Flow-chart of CareToy study according to CONSORT guidelines.** NICU: Neonatal Intensive Care Unit; GA: Gestational Age; IMP: Infant Motor Profile; AIMS: Alberta Infant More Scale; BSID-III Cog: Bayley Scales of Infant Development III- Cognitive Subscale; Teller: Teller Acuity Cards; CTC: CareToy for Clinics; ASQ-3: Ages & Stages Questionnaire Third Edition; S-E BSDI-III: Social-Emotional Scale of Bayley III; PSI: Parenting Stress Index; CA: Corrected Age.

### Study sample and recruitment

The study population will consist of preterm infants recruited at the local Neonatology Units (“Santa Chiara” University Hospital in Pisa and Rigshospitalet in Copenhagen). Eligible infants will be identified according to strict inclusion and exclusion criteria (see below) by the Neonatology teams before the discharge. They will inform the caregivers about the study and, if interested, the information letter and the informative flyer about the project will be given. Recruitment should take place after discharge until 9 months of corrected age. If the parents accept to participate they will provide their written informed consent for the infant to take part of the study. Extensive perinatal data will be collected from medical records and the infants will be evaluated on the basis of a standard neurological examination (Hammersmith Neurological Examination, HINE [28, 29] and by Prechtl’s General Movements Assessment, GMA [30, 31]).

The clinical trial has been approved by the Ethics Committee of Pisa University Hospital (Italy), Tuscan Region Pediatric Ethics Committee (Italy) and to Ethics Committee of Region Hovedstaden (Denmark). Moreover, the Italian Ministry of Health has approved the trial considering that the CareToy is configured as a medical device without a CE mark.

This study will include preterm infants that met the following criteria:

Inclusion Criteria:

 gestational age ≥28 + 0 weeks and 32 + 6 weeks corrected age at baseline: between 3 and 9 months; achievement of predefined cut off scores in gross motor ability derived from Ages & Stages Questionnaire® Third Edition (ASQ-3), in relation to corrected age [32].

In detail:4 months form (from 3 months to 4 months 30 days) score ≥10;6 months form (from 5 months to 6 months 30 days) score ≥5 - <50;8 months form (from 7 months to 8 months 30 days) ≥10 - <30

Exclusion Criteria:

 infants with gestational age <28 weeks or ≥33 weeks infants small for gestational age (i.e. weight below the 10^th^) presence of brain damage i.e. brain malformation, intra-ventricular haemorrhage (IVH) >1; any degree of periventricular leukomalacia (PVL) known epilepsy or other form of seizure severe sensory deficits (blindness, deafness) other severe non neurological malformations participation in other experimental studies having rehabilitation aims

### Sample size

According to CONSORT guidelines [26, 27] the sample size estimates were based on projected treatment effect on the primary outcome measure, the Infant Motor Profile (IMP [33, 34], see below). A sample of 36 infants is required to detect a clinically relevant change of 7.5 points in the total IMP score (SD = 8.2) at significance level of 0.05 and 80% power [35]. Considering a 10% of possible drop-outs a minimum of 40 infants will be recruited. Twins will always be assigned to the same group, in order to facilitate the parents in managing the CareToy system for their infants.

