### Randomisation

After enrolment, infants will be randomly allocated to the intervention (CareToy training) or control group using a computer generated set of random pair 1:1 allocation (CareToy training – standard care or standard care – CareToy training). These random sets will be sealed in numbered envelopes.

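### With the stated inputs, 36 analysable infants fall modestly short of 80% power: 78.3% by the two-sided normal formula (38 needed) and 76.0% by the two-sided t-test (40 needed)

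*Protocol article*

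**What the plan says.** The Sample size section of the protocol article gives the whole calculation in two sentences. The first reads "A sample of 36 infants is required to detect a clinically relevant change of 7.5 points in the total IMP score (SD = 8.2"), and adds "at significance level of 0.05 and 80% power" with a literature citation. The second reads "Considering a 10% of possible drop-outs a minimum of 40 infants will be recruited". The Randomisation section specifies a "computer generated set of random pair 1:1 allocation", which makes 18 infants per arm out of 36.

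Three things are not stated: whether the test is one- or two-sided, which test or formula was used, and whether 8.2 is the SD of the total IMP score or of its change. The section on the primary outcome makes the change from T0 to T1 the primary outcome. The Analyses section names no test for the primary comparison and places basal motor level among the effect modifiers of a second level of analysis.

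**The concern.** A sample size statement lets a reader judge how likely the trial was to miss the effect it was built to find. Here the difference, SD, significance level, power and allocation ratio are all given, so the total can be recomputed, and it does not come out at 36. The usual two-sided calculations need more infants and the one-sided ones need fewer.

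At stake is the type II error. If 36 infants are analysed as planned after drop-out, the chance of missing a true 7.5-point difference is 22% to 24%, not the stated 20%. The trial is small and is offered as first evidence on a new device, so a null result would be read against the stated power.

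**Working it through.** **Inputs.** From Sample size: difference d = 7.5, SD s = 8.2, significance level 0.05, power 80%, 36 analysable, 10% drop-out, 40 recruited. From Randomisation: 1:1, so 18 per arm. Assumed, because not stated: an unadjusted comparison of two independent means, with 8.2 as the between-infant SD of whatever is analysed. Two-sided is taken first, then one-sided.

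**1. The plan's own drop-out step.** 36/(1 − 0.10) = 40. This reproduces.

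**2. Two-sided normal formula.** n per arm = 2 × (1.96 + 0.8416)² × (8.2/7.5)² = 2 × 7.849 × 1.1954 = 18.76. Unrounded, the total is 37.5; rounded up to 19 per arm it is 38. The stated 36 is 2 infants below that.

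Power at 18 per arm: the standard error is 8.2 × √(2/18) = 2.733, and 7.5/2.733 = 2.744. Power = Φ(2.744 − 1.960) = 78.3%.

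**3. Two-sided t-test (noncentral t, 2n − 2 degrees of freedom).**

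| Per arm | Total | Power |
|---|---|---|
| 18 | 36 | 76.0% |
| 19 | 38 | 78.3% |
| 20 | 40 | 80.5% |

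The unrounded requirement is 19.77 per arm, so 20 per arm and 40 in total. With 18 per arm, the difference detectable with 80% power is 7.88, or 7.9 points.

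**4. Does a one-sided test explain 36?** The normal formula gives 2 × (1.6449 + 0.8416)² × 1.1954 = 14.78 per arm, so 30 in total. The one-sided t-test has 78.8% power at 15 per arm and 81.1% at 16, so it needs 32. With 36 infants the power would be 86.4% (normal) or 85.2% (t). A one-sided test therefore overshoots and does not yield 36 as the number required.

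**5. Does rounding of the inputs explain it?** With d anywhere from 7.45 to 7.55 and s from 8.15 to 8.25, the normal formula gives 38 or 40 in total. Power at 36 runs from 77.3% to 79.4% (normal) and from 74.9% to 77.0% (t). None of these reaches 80%. For 36 to be right, the SD would have to be 8.03 (normal) or 7.80 (t).

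**6. Consequence for recruitment.** Under the t-test, 40 is already the number that must be analysable. Keeping 80% power after 10% loss would mean 40/0.9 = 44.4, so 45 recruited.

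**The case against.** The best case for the plan has three parts.

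First, the article names neither the test nor its sidedness, and it cites a source that is not available here. On the normal formula, 36 misses by only 2 infants and under 2 power points; the further step from 38 to 40 is the small-sample t correction. This stands. It means that 76% and 40 must be given as conditional on a two-sided t-test. It does not rescue the figure, because 18.76 per arm cannot be rounded down to 18, and the power at 36 is below 80% by either two-sided route.

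Second, baseline adjustment could close the gap. If 8.2 is the SD of the score, adjusting for baseline multiplies it by √(1 − r²), where r is the T0–T1 correlation. The power at 36 is then about 77.7% for r = 0.2, 79.8% for r = 0.3, 82.9% for r = 0.4 and 86.8% for r = 0.5. The same assumption can also go the other way: an unadjusted change score has SD 8.2 × √(2(1 − r)), giving 61.5% at r = 0.3, 76.0% at r = 0.5 and 84.6% at r = 0.6. These r values are assumptions, since the article gives none. It also mentions no adjustment in the calculation and leaves basal motor level to the second-level analysis. The possibility is a reason to state the basis, and does not show that 36 was derived this way.

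Third, the recruitment figure is a minimum, so more than 40 may be enrolled. That is true, but it does not alter what is claimed for 36.

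A reader might go further and infer that the true power is definitely 76%, or that the trial must enrol 45. The document supports neither. The first needs a test and an SD definition that it does not give; the second treats a gap of 2 to 4 points as unacceptable, when an accurate statement of power would do.

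**Conclusion.** The point holds in a modest, conditional form. On the stated inputs, with an unadjusted two-sided comparison, 36 analysable infants give 78.3% power by the normal formula or 76.0% by the t-test, against 80% claimed; 38 or 40 would be needed. At 18 per arm with an estimated variance, the t-test figure is the one to quote. Recruiting 40 then gives 80% power only if no infant is lost, so the planned drop-out allowance is used up by the too-low base.

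The arithmetic is certain. What is uncertain is whether it matches the calculation that the sponsor ran, because the test, the sidedness and the meaning of 8.2 are unstated. The trial's validity is not affected. The stated power should be corrected.

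**What to change.** Restate the Sample size section along these lines: *36 analysable infants (18 per arm) give about 76% power (two-sided t-test, 0.05) for a between-arm difference of 7.5 points with SD 8.2; the difference detectable with 80% power is 7.9.* Say in the same place whether 8.2 is the SD of the score or of the T0–T1 change. Only the sponsor can supply this, and it should not be filled in by assumption.

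If the calculation relied on a one-sided test or on baseline adjustment, say so, give the assumed T0–T1 correlation where one was used, and report the resulting power instead.

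No extra enrolment is required. The cost is a reworded statement with a slightly less favourable power.

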### Analyses

Clinical Data will be managed and analysed using the Statistical Package for Social Sciences (SPSS). Descriptive statistics (means, standard deviation) will be calculated to summarise the data set for both groups and to identify potential baseline differences between the groups; p values will be used to indicate the strength of the evidence, and the Bonferroni correction for multiple assessments will be performed. The primary level of analysis will be the assessment of the effects of CareToy training at the primary endpoint (T1) in the primary and then in the secondary outcome measures. In the second level analysis we will provide multivariate statistics in order to take into account effect modifiers such as basal level of motor development, family compliance and time of training.

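### Twins are always allocated together, yet the 36 infants are counted as independent, so the stated 80% power is too high if correlated twin pairs enrol

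*Protocol article*

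**What the plan says.** The Sample size section of the protocol article counts in infants. It says "A sample of 36 infants is required" for a "clinically relevant change of 7.5 points in the total IMP score", with an SD of 8.2, "at significance level of 0.05 and 80% power". The only inflation is for attrition: "Considering a 10% of possible drop-outs a minimum of 40 infants will be recruited". The paragraph then adds "Twins will always be assigned to the same group", so that parents can manage the system more easily. It gives no expected twin share, no within-family correlation and no design effect.

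The Randomisation section says that "infants will be randomly allocated to the intervention (CareToy training) or control group", using computer-generated 1:1 pairs in numbered sealed envelopes. It does not say how a twin pair takes up an envelope.

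The Analyses section promises summary statistics ("Descriptive statistics (means, standard deviation) will be calculated to summarise the data set for both groups"), p-values, a Bonferroni correction, an assessment of effect at T1, and a second-level multivariate analysis. The modifiers given as examples for that second level are baseline motor level, family compliance and training time. Neither the test for T1 nor the handling of twins is mentioned.

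**The concern.** Co-twins share gestation, home and caregivers, and the reason given for keeping them together implies that they share the CareToy system too. A positive correlation between their IMP changes from T0 to T1 is the natural expectation. Because both are in the same arm, that correlation adds to the variance of the difference between arms. Two co-allocated twins then carry less information than two unrelated infants.

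Two things are at stake. The first is the stated power, which the document fixes and which an analysis plan cannot restore. The second is the validity of the T1 test, which depends on an analysis that the article does not specify. The trial has about 40 infants, so a few twin pairs per arm are a noticeable fraction of the data.

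**Working it through.** **Inputs from the Sample size and Randomisation sections.** Difference d = 7.5, SD s = 8.2, alpha 0.05, power 80%, 36 analysable infants allocated 1:1 (18 per arm), 10% drop-out. The article does not say whether the test is two-sided (assumed here), or whether 8.2 is the SD of a score or of a change (used as given).

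**Reproducing the plan's figure.**
- Normal formula for two independent groups: n per arm = 2 × (s/d)² × (1.960 + 0.842)² = 18.76. This rounds up to 19 per arm, 38 in total, against 36 stated. Power at 18 per arm is 78.3%.
- Two-sided t-test: 20 per arm, 40 in total. Power at 18 per arm is 76.0%.
- One-sided normal formula: 30 in total, which does not fit.
- Drop-out: 36 / 0.9 = 40, as stated.

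So 36 is approximately the two-sided result for independent infants with a design effect of 1. It lies slightly below what its own inputs require, before any twins are considered.

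**Design effect.** Let f be the share of infants in twin pairs and ρ the within-pair ICC. An arm of n infants has fn/2 pairs, and each pair adds 2ρs² to the variance of the arm total. The variance of the arm mean is therefore (s²/n)(1 + fρ), so DE = 1 + fρ. Neither f nor ρ is in the document; the values below are assumptions.

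**Power at 18 per arm.** Noncentral t with 34 df, noncentrality d / (s × √DE × √(2/18)), which is 2.744 at DE = 1:

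| f | ρ | DE | Effective infants (36/DE) | Power | Loss due to twins |
|---|---|---|---|---|---|
| 0 | – | 1.00 | 36 | 76.0% | – |
| 0.1 | 0.3 | 1.03 | 35 | 74.8% | 1 point |
| 0.2 | 0.4 | 1.08 | 33 | 72.7% | 3 points |
| 0.3 | 0.6 | 1.18 | 31 | 68.9% | 7 points |
| 0.4 | 0.8 | 1.32 | 27 | 64.1% | 12 points |

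If all 40 recruited infants were analysed (20 per arm), power would be about 77% at DE 1.08 and 69% at DE 1.32. The drop-out allowance does not absorb the loss at those values.

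**Type I error if, and only if, the T1 test ignored twin pairs.** Simulated unadjusted t-test, 18 per arm, no treatment effect:

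| Twin pairs per arm | Share of infants | ICC | Type I error |
|---|---|---|---|
| 1 | 11% | 0.3 | about 5.5% |
| 2 | 22% | 0.4 | about 6.1% |
| 3 | 33% | 0.6 | about 7.4% |
| 4 | 44% | 0.8 | about 9.4% |

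The last row goes a little beyond the 40% share used for power. At 40% and ICC 0.8 the large-sample formula 2 × (1 − Φ(1.96/√1.32)) gives 8.8%.

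**The case against.** The strongest reply concerns the analysis. A reader might infer that the plan treats every infant as independent at T1 and that the p-value will therefore be too small. The article does not support this: it names no T1 test, and the sentence on means and SDs is descriptive. A full protocol or analysis plan, not shown, could specify clustering by family. This objection stands, so the type I error figures are conditional.

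A reader might also see a contradiction between pairwise 1:1 allocation of infants and the rule for twins. The pairs read naturally as blocks of two, and a twin pair can occupy one slot. What is missing is a sentence saying so. This too stands; it is an unstated detail to reconcile, not a proven conflict.

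Third, comparing 64% to 73% with the stated 80% would blame twins for too much. About 4 points of that gap are present with no twins, since t-test power at 36 infants is 76.0%. Finally, if very few pairs enrol the effect is small: about 1 power point with 10% twins and ICC 0.3.

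None of this removes the sample-size point. The count of 36 and the co-allocation rule stand in the same paragraph, and a family-clustered analysis would correct the p-value without restoring the claimed power.

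**Conclusion.** The point holds for the sample size. The stated 80% rests on independent infants, while the plan's own rule makes the family the allocated unit for multiples. Power is overstated whenever twin pairs enrol and their IMP changes correlate positively. Twins themselves cost about 1 to 12 points at 36 infants, from a t-test baseline of 76.0%, over assumed shares of 10% to 40% and ICCs of 0.3 to 0.8. The document does not allow the loss to be fixed more closely.

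For the analysis, only a conditional statement is justified: type I error would be about 5.5% to 9.4% if twin pairs were ignored. The document does not establish that they will be.

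**What to change.** 1. In the Randomisation section, state that each family receives one allocation and that a twin pair uses one envelope, so that this section agrees with the rule under Sample size.
2. In the Analyses section, specify that the T1 primary comparison accounts for family: a linear mixed model with a random family intercept, or GEE clustered on family, in either case with a small-sample correction because pairs will be few.
3. Under Sample size, restate the power at 36 analysable infants over a declared range of twin share and ICC, as in the table above, starting from the no-twin value.

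The cost is a less favourable stated power and slightly wider intervals. No extra infants or visits are needed for these changes. They make the power claim accurate; they do not bring it back to 80%.
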